#### **15.1.5. Safety analysis**

##### **15.1.5.1. AEs**

AEs are defined as all harmful and unintended signs (e.g.: abnormal laboratory values), symptoms or diseases which occur in patients who are treated with the investigational product. It is not that AEs should always have a causal relationship with the investigational product. However, changes that originate from the progress or occurrence of normal disease are not considered AEs if the frequency and seriousness is not seriously different from the expected level. Whether there are differences in the incidence rate of AEs between groups will be analyzed using the Pearson's chi-square test or the Fisher's exact test. In addition, frequency, percentage, and number of incidence regarding AEs will be presented by physical organ and recommended term for each group.

##### **15.1.5.2. Laboratory tests**

With regard to whether each laboratory test result has any change after the termination of the investigational product use versus before treatment (screening), the descriptive statistics of the results observed will be presented per administration group. At the termination of the investigational product use versus before treatment (screening), in addition, whether there is any difference in variation between groups will be analyzed. Regarding laboratory tests, intragroup and intergroup comparisons will also be carried out.

- Intragroup comparison: For continuous variables, the descriptive statistics describing baseline, value at end time, and difference between baseline and end time will be presented; and the mean variation will be analyzed using the paired t-test or the Wilcoxon's signed rank test. For categorical variables, a contingency table will be completed, and it will be analyzed using the McNemar's test.

- Intergroup comparison: For continuous variables, difference between baseline and end time will be compared and analyzed using the ANOVA or the Kruskal-Wallis test. For categorical variables, homogeneity between treatment groups will be analyzed using the Pearson's chi-square test, the Fisher's exact test, etc.

With regard to each laboratory test result, in addition, the frequency and ratios of patients, who turn normal/ clinically non-significant abnormality into clinically significant abnormality from

before treatment (screening) to the termination of the investigational product use, will be presented for each treatment group.

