|                    | Sample size including dropout rate (20%)                                                                                                                                                                                                                                                                                                                                                                                                                                                                                                                                                                                                                                                                                                                                                                                                                                                                                                                                                                                                                                                                                                                                                                                                                                                                                                                                                                                                                                               | 30                | 30                | 30            |

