## 2) Laboratory tests

The laboratory tests will be conducted on all patients at Visits 1, 9 and 15 to assess their systemic health status. All of the inclusion criteria and exclusion criteria, including clinical laboratory test results, must be checked before the administration of the investigational product. Clinically significant abnormal results at the time of screening will be recorded as a medical history, and subsequent clinically significant abnormal results will be recorded as an adverse event.

In addition to evaluations according to the schedule, additional tests are possible if the investigator judge as necessary.

In case of a visit scheduled for blood sampling prior to clinical laboratory tests, fasting (drink and food prohibition except water) is required to patients. As for the screening (Visit 1) test, if there are results of a test conducted within 4 weeks, they can be used. In addition, reexamination can be carried out according to the investigator's judgment. Test items include:

- Hematological tests : WBC, RBC, Hemoglobin, Hematocrit, Platelets count, WBC Diffcount (Neutrophils, Lymphocytes, Monocytes, Eosinophils, Basophils)
- Blood Chemistry : BUN, Creatinine, Uric acid, Total bilirubin, Albumin, Total Protein, ALT, AST,  $\gamma$ -GTP, Alkaline phosphatase, Glucose, Total Cholesterol \*Only during screening visits: Vitamin B12, Folic acid, HbA1c
- Urinalysis : Protein (Albumin), Glucose, Ketones, WBC, Blood (RBC)
- Blood coagulation test : INR (Only during screening visits)
- Thyroid function tests : TSH, free T4 (Only during screening visits)
- Syphilis, AIDS tests : VDRL, anti-HIV (Only during screening visits)

Serum creatinine clearance is determined at the time of screening using the following Cockcroft-Gault formula.

---

$$CL_{cr} = \frac{[(140 - \text{Age (years)}) * \text{Weight (kg)} * 0.85(\text{for female patients})]}{72 * \text{Serum Creatinine (mg/dl)}}$$

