#### **15.1.5.4. Physical examination**

For physical examinations, comparisons will be made between the physical examination results measured after the termination of the investigational product use versus before treatment (baseline), and then this will be summarized in frequency and percentage for each administration group to identify normality (including NCS)/ CS changes.

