#### **15.1.6. Handling of dropouts or missing values**

If a patient who drops out of this clinical trial appears, the cause and date of dropout should be recorded in the CRF and the medical chart. If a missing value of data occurs during FAS analysis or a patient drops out of the clinical trial before its termination, the most recently

obtained data will be analyzed as if it was obtained at that relevant time (Last Observation Carried Forward Method).

However, LOCF will not be applied for PPS analysis. In case of safety evaluation items, the missing values will not be replaced.

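### The laboratory shift count in Section 15.1.5.2 leaves out the Week 12 panel, so the per-test shift table is incomplete, although adverse event reporting still captures these results

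*Protocol*

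**What the plan says.** Protocol Section 12.1.2, item 2 (Laboratory tests), sets the schedule: "The laboratory tests will be conducted on all patients at Visits 1, 9 and 15 to assess their systemic health status". Visit 1 is screening, Visit 9 is Week 12 and Visit 15 is Week 24. The item also allows extra tests at the investigator's discretion. It directs that clinically significant abnormal results after screening be recorded as adverse events.

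Section 15.1.5.2 then defines the laboratory analysis by two time points. Descriptive change is from screening to the end of product use. The between-group analysis is framed the same way: "At the termination of the investigational product use versus before treatment (screening), in addition, whether there is any difference in variation between groups will be" analysed. The within-group and between-group tests act on the difference between baseline and end time. The shift count is described as "the frequency and ratios of patients, who turn normal/ clinically non-significant abnormality into clinically significant abnormality from", and the sentence goes on to name the same two points, screening and the end of dosing. The denominator of those ratios is not stated.

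Section 15.1.6 adds: "In case of safety evaluation items, the missing values will not be replaced". Section 15.1.5.4 uses a similar before-and-after comparison for physical examination, although the flow chart schedules an examination at every visit. For vital signs, by contrast, Section 15.1.5.3 asks for descriptive statistics at each visit.

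**The concern.** The Week 12 panel is the only scheduled on-treatment laboratory assessment before the end of dosing, and the protocol assigns it to no laboratory summary. Two kinds of patient are affected:

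- A patient who is clinically significant on a test at Visit 9 and normal again at the end appears in the table as having had no shift.
- A patient who is clinically significant at Visit 9 and has no end panel cannot be placed in the table, because the Visit 9 result is not carried to the end point.

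Laboratory tests are a listed safety endpoint (Section 6.3), and safety is part of the primary objective (Section 6). A reader of the shift table would naturally want to know how many patients became clinically significant on each test at any time on treatment. As defined, the table answers a narrower question: how many were in that state at the end.

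**Working it through.** **1. Where each panel is used**

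| Panel | Drawn (12.1.2) | Used in 15.1.5.2 |
|---|---|---|
| Visit 1, screening | yes | yes, as the starting value |
| Visit 9, Week 12 | yes | not named in any summary |
| Visit 15, Week 24, or exit | yes | yes, as the end value |
| Unscheduled | allowed | not named |

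**2. What the shift count leaves out.** For one test in one arm, take patients who are normal or NCS at screening and consider the scheduled panels. Let

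- E = number clinically significant at the end panel (the protocol's count);
- R = number clinically significant at Visit 9 but not at the end panel;
- M = number clinically significant at Visit 9 with no end panel.

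The number clinically significant at any scheduled post-dose panel is A = E + R + M, so the end-only count falls short by A − E = R + M. This is never negative, and it is zero when R = 0 and M = 0. The protocol gives no laboratory abnormality rate, resolution rate or missing-panel rate, so R and M cannot be calculated from it.

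**3. How wide the missing-panel route is.** The one related figure is the dropout allowance, which reproduces: 24 / (1 − 0.20) = 30 per arm and 72 / (1 − 0.20) = 90 in total. Planned dropout is thus 30 − 24 = 6 per arm. That is not the number without an end panel. Sections 12.2.7 and 14.1 ask patients who drop out to have the Visit 15 tests, which include the laboratory panel. If all, half or none of the 6 attend, then 0, 3 or 6 per arm lack an end panel, and only those who were also clinically significant at Visit 9 enter M. The route remains mainly for withdrawal of consent, after which Section 14.1 rules out further data collection, and for loss to follow-up.

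**4. Count and percentage behave differently.** If the denominator is patients with an end panel, those without one leave both numerator and denominator. If missingness is unrelated to the result, the expected end-of-treatment percentage does not change. The percentage is distorted by this route only if missingness is linked to the result, about which the protocol gives no information. Resolution (R) removes a patient from the numerator and keeps that patient in the denominator, so it is the clearer mechanism.

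**5. Where the missed results still appear.** Section 12.1.2 sends clinically significant laboratory results after screening to the adverse event record, and does the same for physical examination findings that meet the adverse event definition. Section 15.1.5.1 tests adverse event incidence between groups and tabulates events by organ and term.

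**The case against.** The strongest reply is that nothing is lost. A Week 12 abnormality that resolves is still an adverse event, still tabulated and still in the between-group comparison. An end-of-treatment shift table is a legitimate summary of persistent change, and the protocol does not claim that it estimates any-time incidence. Early leavers are asked for an exit panel, which serves as their end value. Visit-level laboratory tables are often left to the SAP, and Section 15.1.5.2 does not forbid them.

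Most of this stands, and it limits the point to the shift table. Two things remain. First, the protocol states a shift rule; it does not leave the matter open. Second, adverse event tables do not replace a per-test shift count: Section 16.2 asks for a comprehensive diagnosis or symptom rather than each sign, so several abnormal tests may be merged under one term.

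It could also be argued that the phrase running from screening to termination describes a period, which would include Visit 9. The rest of the section works with baseline and end time, so two time points is the natural reading. If a period is meant, the text should say so.

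**Conclusion.** The point holds as a minor one. On its natural reading, Section 15.1.5.2 omits Week 12 abnormalities that resolve from the per-test shift table, and it cannot score patients who have no end panel. The shortfall in the count is R + M per test and arm. Its size is not derivable from the protocol and may be zero. The primary efficacy analysis and adverse event capture are unaffected.

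A reader might infer more than the text supports:

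- **That the safety analysis understates harm.** It does not follow, because the same results enter the adverse event analysis.
- **That the shift table would contradict the adverse event listing.** An end-of-treatment state and an any-time incidence are different quantities and may properly differ.
- **That the planned 20% dropout translates into lost shifts.** Dropouts are asked for the Visit 15 panel, and the effect on the percentage depends on an unstated denominator.
- **That transient injection-site reactions show the same flaw in the physical examination table.** Section 13 says they arise within 24 hours and clear within days, while visits are one or two weeks apart. Counting findings at any visit would miss many of them too; adverse event reporting is their route.

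**What to change.** In Section 15.1.5.2, define the shift as normal or NCS at screening and clinically significant at any post-dose panel: Visit 9, Visit 15 or exit, or unscheduled. State the denominator as patients with a screening panel and at least one post-dose panel. Keep the screening-to-end shift as a second column, and add Visit 9 descriptive statistics, matching the by-visit treatment of vital signs. Optionally, apply the same any-post-dose count to physical examination in Section 15.1.5.4.

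The cost is wording and one more column. The data are already collected, and no visit or test is added. Where Week 12 abnormalities resolve, shift rates will look slightly less favourable, and this applies to all arms.

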#### **15.1.5.3. Vital signs**

For vital signs, the descriptive statistics will be presented for each time point of visit. With regard to whether there is any change after the termination of the investigational product use compared to before treatment (screening), the descriptive statistics of the results observed will be presented.

At the termination of the investigational product use compared to before treatment (baseline), in addition, whether there is any difference in variation between groups will be analyzed. Regarding vital signs, intragroup and intergroup comparisons will also be carried out.

- Intragroup comparisons: For continuous variables, the descriptive statistics describing baseline, value at end time, and difference between baseline and end time will be presented; and the mean variation will be analyzed using the paired t-test or the Wilcoxon's signed rank test. For categorical variables, a contingency table will be completed, and it will be analyzed using the McNemar's test.
- Intergroup comparisons: For continuous variables, difference between baseline and end time will be compared and analyzed using the ANOVA or the Kruskal-Wallis test. For categorical variables, homogeneity between treatment groups will be analyzed using the Pearson's chi-square test, the Fisher's exact test, etc.

#### **15.1.5.4. Physical examination**

For physical examinations, comparisons will be made between the physical examination results measured after the termination of the investigational product use versus before treatment (baseline), and then this will be summarized in frequency and percentage for each administration group to identify normality (including NCS)/ CS changes.

#### **15.1.6. Handling of dropouts or missing values**

If a patient who drops out of this clinical trial appears, the cause and date of dropout should be recorded in the CRF and the medical chart. If a missing value of data occurs during FAS analysis or a patient drops out of the clinical trial before its termination, the most recently

obtained data will be analyzed as if it was obtained at that relevant time (Last Observation Carried Forward Method).

However, LOCF will not be applied for PPS analysis. In case of safety evaluation items, the missing values will not be replaced.

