### **7.6.2. Prohibited concomitant medications and therapy**

The following concomitant medications are prohibited from screening (visit 1) to end-of-study visit.

Prohibited items are not limited to the concomitant medications and combination therapies specified below, and any medications judged by the investigator to have an effect on evaluating the efficacy of this clinical trial can also be prohibited.

If the prohibited concomitant medications need to be used for the treatment of patients over the duration of this clinical trial according to the judgment of investigators or doctors in charge

of other medical symptoms, the patients should immediately discontinue this clinical trial and this will have to be recorded in detail in the CRF.

- ① Other drugs for AD other than donepezil : Acetylcholinesterase inhibitors (rivastigmine, galantamine, etc.), NMDA receptor antagonists (memantine, etc.)
- ② Choline excitatory drugs (However, drugs for local administration such as choline agonists and pilocarpine collyrium are allowed.)
- ③ CNS stimulants (Methylphenidate, Modafinil, Pemoline, Atomoxetine)
- ④ Antidepressant drugs (tricyclic antidepressants, MAO inhibitors)
- ⑤ Typical antipsychotic drugs (Bromperidol, Chlorpromazine, Haloperidol)
- ⑥ Anticholinergic drugs (Atropine, Glycopyrrolate, Scopolamine, Homatropine, Ipratropium)  
However, the short-term use for the purpose of alleviating the symptoms of digestive system is allowed.)
- ⑦ All investigational products or medical devices not specified in this trial.
- ⑧ Use of any abused drug (including but not limited to illegal amphetamines, hemp, cocaine, illegal opiate drugs, propoxyphene, methadone, methaqualone, phencyclidine or illegal barbiturates)
- ⑨ Previous administration of all investigational vaccines for AD
- ⑩ Regular use of narcotics (for 3 days or more a week)
- ⑪ Other drugs affecting the immune system

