#### **12.1.1.1. SIB (Severe Impairment Battery)**

SIB evaluation will be conducted at Visits 2, 9 and 15.

The SIB (Saxton et al., 1990) was developed to evaluate dementia patients with severe cognitive impairment and consists of easy and simple questions. The questionnaire consists of 50 questions for the 9 items of "orientation", "social interaction", "construction", "orienting to name", "language", "memory", "praxis", "visuo-spatial ability". The scores range from 0 to 100 points, and the better the state of the patient, the higher the score.

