**12.2.7. Visit 15 (24 weeks  $\pm$  3 days ; Administration of the Investigational Product)**

This visit will be conducted at 24 weeks after Visit 1, and evaluations to be made at this visit are as follows. Even the patients who drop out of this clinical trial should undergo the tests conducted at Visit 15.

- 1) Any change in concomitant medication will be checked in comparison to last visit.
- 2) Physical examination will be carried out.
- 3) Vital signs (blood pressure, pulse rate, respiration, and body temperature), height, and body weight will be measured.
- 4) Laboratory tests will be conducted.
- 5) SIB test will be conducted.
- 6) K-MMSE test will be conducted.
- 7) CDR-SOB test will be conducted.
- 8) CIBIC-Plus test will be conducted.
- 9) NPI test will be conducted.
- 10) GDS test will be conducted.
- 11) ADCS-ADL-severe test will be conducted.
- 12) Incidence of AEs and the details will be investigated.
- 13) The investigational product will be administered (Whether there is any AE will be observed for 30 minutes after the administration).
- 14) For female patients of childbearing age, pregnancy test will be conducted.
- 15) The next visit date (Visit 16) will be set.

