## **15. STATISTICAL ANALYSIS METHOD**

### **15.1. Statistical Analysis Plan**

#### **15.1.1. Definition of Analysis Set**

Analysis set is defined as follows:

- 1) Safety analysis set: the patients who have been randomized and undergone safety evaluation once or more among those who have been administered the investigational product at least once.
- 2) FAS (Full Analysis Set): the patients whose data of primary efficacy variable can be obtained among those who have been administered the investigational product at least once.
- 3) PPS (Per-Protocol Set): the patients who have completed this trial without violation of the protocol among those included in FAS group.

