#### **15.1.2. General principle of statistics**

All statistical significance tests will be conducted in the form of 2-tailed tests at the 5% significance level ( $\alpha$ ).

The major analysis of efficacy data obtained from the patients participating in this clinical trial will be carried out in the FAS in principle.

The analysis of safety data is carried out on the Safety analysis set.

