#### **15.1.7. Handling of protocol violations**

The principal investigator and the subinvestigator should be well-acquainted with the protocol and thoroughly carry out the clinical trial procedures as specified in the protocol so that any protocol violation does not occur. In order to comply with the schedules for the administration of the investigational product and tests in this clinical trial, the investigator should take appropriate measures, such as written notification or telephone monitoring related to visit time, so that the patient can attend the visit on the date. On the other hand, the inevitable protocol violation should be handled as follows:

In case of a serious violation of the clinical trial protocol, the patient should be eliminated from the analysis (excluding PPS). Refer to the items below:

- ① In case the patient has no signed consent form.
- ② In case the patient is found to have violated the inclusion/exclusion criteria
- ③ In case the patient took the prohibited concomitant medication over the duration of clinical trial
- ④ In case the primary efficacy evaluation tests at the time of the initiation-termination of this trial were missing.

When it comes to minor protocol violations, which are judged to have no effect on the interpretation of the clinical trial results, the degrees and causes of violations or delays should be exactly recorded. Whether this affected this clinical trial will be comprehensively considered through the blind meeting prior to Database Lock, and will be included in the PPS analysis.

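### LOCF in the main analysis scores a dropout's earlier SIB as a Week-24 value in a progressive disease; the resulting distortion depends on who leaves and when

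*Protocol*

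**What the plan says.** Protocol 15.1.2 sets the main set: "The major analysis of efficacy data obtained from the patients participating in this clinical trial will be carried out in the FAS in principle". For missing data or dropout in that set, 15.1.6 has the most recently "obtained data will be analyzed as if it was obtained at that relevant time (Last Observation Carried Forward Method"). The primary test (15.1.4.1) is a t-test or rank-sum test on the change in SIB from baseline to Visit 15, Week 24.

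The values available to carry follow from 12.1.1.1: "SIB evaluation will be conducted at Visits 2, 9 and 15", that is, baseline, Week 12 and Week 24. Section 12.2.7 adds an exit assessment: "Even the patients who drop out of this clinical trial should undergo the tests conducted at Visit 15". Section 14.1 repeats the request, but also says that nothing more can be collected once consent is withdrawn.

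Section 15.1.6 makes one exception: "LOCF will not be applied for PPS analysis". The PPS is limited by 15.1.1 to patients who completed the trial without violation, and 15.1.7 lists this among the serious violations: "In case the primary efficacy evaluation tests at the time of the initiation-termination of this trial were missing".

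The FAS itself is defined in 15.1.1 as "the patients whose data of primary efficacy variable can be obtained among those who have been administered the investigational product at least once". It does not say which SIB value is needed. Section 9.3 gives the purpose as reducing disease progression, and plans for 20% dropout in every arm.

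**The concern.** In a disease where scores fall over time, carrying an earlier score forward assumes that decline stopped on the day the patient left. That is the quantity the trial is meant to measure. A patient who leaves before Week 12 without an exit test would be scored as a change of zero, which is better than an average completer would score. Less time on study then looks like benefit.

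The two dose-placebo differences at Week 24 are therefore partly a function of dropout. A filled-in value is also treated as if it had been observed. The PPS offers no cross-check, because it omits the patients in question.

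Unequal dropout is possible here. Section 13 reports injection-site reactions as frequent with GV1001, and 14.1 makes adverse events a ground for withdrawal.

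**Working it through.** **The plan's own figure.** 24 evaluable per arm at 20% dropout: 24/(1 − 0.20) = 30 per arm, 90 in total. This reproduces 9.3. It means 0.20 × 30 = 6 patients per arm are expected to be lost. The protocol gives no effect size, SD or rate of decline, so there is no power figure to reproduce.

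**Assumptions (not in the protocol).** Linear decline of D points over 24 weeks on placebo and D − δ on the dose, where δ is the true benefit. Dropout proportions are dp (placebo) and da (dose). f is the share of the 24-week change already present in the carried value: f = 0 if baseline is carried, 0.5 if Week 12 is carried. Two average cases:
- No exit SIB, half of dropouts before Week 12 and half after: f = (0 + 0.5)/2 = 0.25.
- Exit SIB obtained, exit times uniform over 24 weeks: f = 0.5.

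**Formula.** Expected LOCF difference = D[1 − dp(1 − f)] − (D − δ)[1 − da(1 − f)].

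**Equal dropout d.** This reduces to δ[1 − d(1 − f)]. At d = 0.20 the estimate is 80% of δ for f = 0, 85% for f = 0.25 and 90% for f = 0.5. A true 5 points becomes 4.25 without exit SIBs and 4.5 with them. If δ = 0 the bias is 0.

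**Unequal dropout, no true effect.** The formula becomes D(1 − f)(da − dp). With da = 0.30 and dp = 0.10:

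| D | No exit SIB (f = 0.25) | Rejection | Exit SIB (f = 0.5) | Rejection |
|---|---|---|---|---|
| 3 | +0.45 | 5.3% | +0.30 | 5.1% |
| 6 | +0.90 | 6.6% | +0.60 | 5.5% |
| 9 | +1.35 | 8.3% | +0.90 | 6.3% |

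Positive values favour the dose arm. Reversing the rates reverses the sign. Rejection is the simulated two-sided t-test rate at nominal 5% (30 per arm, SD of change 10). Across simulation runs the bias was 0.43–1.38 points without exit SIBs and about 0.25–0.9 with them; the highest rejection rate seen was 8.8%, at D = 9 without exit SIBs.

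**Equal rates, different timing.** With different carried shares fa (dose) and fp (placebo), the null bias is D[da(1 − fa) − dp(1 − fp)]. For 20% in both arms, D = 6, fa = 0 and fp = 0.5: 6 × (0.20 − 0.10) = +0.6 for the arm that loses patients earlier.

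**Unequal dropout, true effect δ = 3, D = 6.**
- 30% dose, 10% placebo: f = 0.25 gives 6(0.925) − 3(0.775) = 3.23; f = 0.5 gives 6(0.95) − 3(0.85) = 3.15. The effect is inflated.
- 10% dose, 30% placebo: f = 0.25 gives 6(0.775) − 3(0.925) = 1.88; f = 0.5 gives 6(0.85) − 3(0.95) = 2.25. The effect is diluted by 25–38%.

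**The case against.** **The bias is small against the noise.** With SD 10 and 30 per arm, the standard error of a difference is 10 × √(2/30) = 2.58 points. A bias of 0.3–0.9 is about 0.1–0.35 standard errors. Section 11.1 calls the trial a pilot for therapeutic exploration, and 9.3 says its size was not set statistically. This stands, and it limits the severity.

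**The exit SIB helps.** It does: it cuts the null bias by about a third in the scenarios above. It does not remove it, because a test taken in Week 8, say, is still analysed as Week 24, and it cannot be obtained after consent is withdrawn.

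**The FAS may require a Week-24 SIB.** The wording in 15.1.1 allows that reading, and LOCF would then have little to act on for SIB. But 15.1.6 expressly applies LOCF to FAS patients who drop out, so that reading largely empties the protocol's own rule. The two sections need to be reconciled either way.

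**Stronger readings.** A reader might infer that LOCF always dilutes the effect, or that it always raises the false-positive rate. Neither follows. With similar dropout and no effect there is no bias, and with more loss on the dose a real effect can be inflated. A reader might also infer that no other missing-data analysis is planned. The protocol does name the PPS without LOCF, and further sensitivity analyses may be in a statistical analysis plan that was not available. The point is the rule the protocol fixes for its main analysis.

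**Conclusion.** The concern holds in conditional form. The protocol fixes LOCF for the main analysis of a declining outcome, and its only named analysis without LOCF is restricted to completers.

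- Similar dropout across arms, at the planned 20%: a real effect is diluted by 10–20%; no bias under no effect.
- More or earlier dropout in one arm: that arm is favoured, and an apparent drug effect can be created or inflated if it is the dose arm. For 30% against 10% dropout and no true effect, the bias is about 0.25–0.9 points with exit SIBs and 0.4–1.4 without, with two-sided rejection of about 5–6% and 5–9%.

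These sizes rest on an assumed linear decline of 3–9 points, SD 10, and the assumed dropout rates and exit times. The protocol gives none of these except the common 20% rate. The upper figures need the steepest decline, a 20-point imbalance and no exit SIBs together, so they are not a forecast. For an exploratory trial this is a change that should be made. It does not by itself invalidate the design.

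**What to change.** 1. In 15.1.4.1 and 15.1.6, make the primary analysis a likelihood-based repeated-measures model of SIB, with the Week-24 dose-placebo contrast as primary. Enter baseline SIB as a response with its mean constrained equal across arms, so that patients with only a baseline value still contribute.
2. Prespecify how exit SIBs enter: by visit windows or by a continuous-time model. They should never count as Week 24 by default. A model with only fixed visits has no place for a test at an arbitrary time, so this choice has to be written down.
3. State in 15.1.1 that FAS entry does not require a Week-24 SIB, so that it agrees with 15.1.6.
4. Keep LOCF as a sensitivity analysis and add one missing-not-at-random analysis, delta-adjusted or reference-based.

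The cost is protocol wording and some programming. The SIB assessments are already scheduled, so no new visits are needed. The downside is that the model assumes data are missing at random, which the added analysis probes. The change should be made before unblinding, since a later change of method would look data-driven.
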